#### **5.2.3 End of Treatment and/or End of Study Visit (as applicable)**

#### **5.2.4 The end of trial is defined as when the “one-month post-partum questionnaires” has been received from all participants, but not**

A woman can withdraw from the study at any time, and will still receive treatment before and after birth as per ward procedure. Time to delivery, mode of delivery and dose of oxytocin will be recorded, at the discretion of the woman.

#### **5.2.5 After End of Treatment (Follow-up)**

Follow-up information will be obtained one month after delivery by a standardized questionnaire measuring experience of labor and birth.

### **5.3 Criteria for Participant or Treatment Discontinuation**

Participants may be discontinued from study treatment. Specific reasons for discontinuing treatment for this study are:

- Safety reason as judged by the Principal Investigator
- Incorrect enrolment i.e., the participant does not meet the required inclusion/exclusion criteria for the study
- Deterioration in the participant's condition which in the opinion of the Principal Investigator warrants study medication discontinuation (to be recorded as an AE or under Investigator Discretion)
- Voluntary discontinuation by the participant who is at any time free to discontinue her participation in the study, without prejudice to further treatment.

### **5.4 Procedures for Discontinuation**

#### **5.4.1 Patient Discontinuation**

All patients randomized will be included in the study population.

Patients who are randomized in spite of not fulfilling all of the inclusion criteria or fulfilling one or several exclusion criteria can be replaced. Patients who withdraw from the study after randomization cannot be replaced.

If the patient consents, end of study information will be obtained and recorded.

#### **5.4.2 Treatment Discontinuation**

If treatment was discontinued, all study assessments as described in this protocol should be recorded.

#### **5.4.3 Trial Discontinuation**

The whole trial may be discontinued at the discretion of the PI or the sponsor in the event of any of the following:

- Occurrence of AEs unknown to date in respect of their nature, severity and duration

- Medical or ethical reasons affecting the continued performance of the trial
- Difficulties in the recruitment of patients

The sponsor and principal investigator(s) will inform all investigators, the relevant Competent Authorities and Ethics Committees of the termination of the trial along with the reasons for such action. If the study is terminated early on grounds of safety, the Competent Authorities and Ethics Committees will be informed within 15 days.

## **6 ASSESSMENTS**

### **6.1 Assessment of Efficacy Response**

The following parameters will be recorded:

Duration of labor from the time when the participant was given IMP to delivery

Duration of labor from the onset of active labor (at least 3 cm dilatation) to delivery

Duration of the active phase of first stage of labor (at least 3 cm dilatation), from the time when it was noticed that the alert-line of the partogram was crossed (between 3 cm and 9 cm dilatation) and the participant was given IMP, to 10 cm dilatation, or emergency cesarean delivery.

Mode of delivery – spontaneous vaginal delivery, vacuum delivery, forceps delivery, emergency cesarean delivery

Indication for operative delivery

Amount of oxytocin given measured as

1. total time with treatment

2. International Units (IU) (the midwife measures mL of oxytocin solution given during labor. IU are calculated based on standardized concentration of the infusion solution [10 IU oxytocin in 1000 mL NaCl solution])

Apgar score at 5 minutes and 10 minutes after delivery

Admission to the Neonatal Intensive Care Unit

Pain scores using a Visual Analogue Scale at baseline and 30 minutes after administration of IMP

Birth experience measured by the validated questionnaire Child Birth Experience Questionnaire

Maternal heart rate – continuous registration at least 30minutes from administration of IMP

Fetal heart rate - continuous registration at least 30minutes from administration of IMP

Urinary retention

Anal sphincter injury

Postpartum hemorrhage

### **6.2 Safety and Tolerability Assessments**

Safety will be monitored by the assessments described below as well as the collection of AEs. Significant findings that are present prior to the signing of informed consent must be included in the

relevant medical history/ current medical condition page of the CRF. For details on AE collection and reporting, refer to Section 7.5.

For the assessment schedule refer to Flow chart in Section 5.

Physical examination will include an examination of general appearance.

Vital signs mother include blood pressure and pulse.

Vital signs fetus include continuous fetal heart rate tracing.

Maternal height and body weight will be obtained from the pregnancy chart.

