## **3 STUDY POPULATION**

### **3.1 Selection of Study Population**

Academic hospital in Norway. Primiparous women who are giving birth at Department of Obstetrics Rikshospitalet, Oslo University Hospital are invited to participate.

The women will be invited approximately six weeks prior to their due date (gestational week 30), and will receive a mailed invitation letter. In the letter, they will be given opportunity to actively opt out of inclusion. At this time, women may give informed consent to participate, or they can be included when they arrive at the delivery ward. All women will have the opportunity to talk to a midwife or doctor before they give written informed consent, and contact information will be provided in the invitation. The Principal Investigator will sign the consent form.

Women who have received and understood information about the study and are willing to participate prior to start of labor may be included and sign the informed consent form when they arrive at the hospital to give birth.

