## **5.2 By Visit**

### **Informed consent**

All participating women will sign an informed consent during pregnancy. They will receive the invitation to participate in the study six weeks before their due date if they are primiparous, planning a vaginal delivery, and are going to give birth at Oslo University Hospital Rikshospitalet. The laboring women and their fetuses will be monitored after inclusion using CTG (cardiotocography) and measurement of the maternal heart rate for 30 minutes after the treatment is initiated. Patient reported side effects (maternal) will be registered in the CRF based on a list of symptoms. Occurrence, degree and duration of side effects will be registered within 30 minutes after the treatment is given. Treatment of side effects will be registered. All women will be asked to assess labor pain before initiation of the treatment, and 30 minutes after initiation of the treatment, as well as to fill in a validated questionnaire on birth experience one month after delivery.

Informed consent must have been given voluntarily by each woman before any study specific procedures are initiated. The following data will be retrieved from the participants' medical charts and pregnancy charts:

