#### **5.2.1 Before Treatment Starts**

- Eligibility will be assessed by the inclusion chart
- Baseline is defined as the time point in labor when slow progress is detected. At baseline, vital signs from mother and fetus will be obtained, and we will perform baseline observations regarding medical history
- For the endpoint pain baseline measurements by a VAS scale will be obtained before randomization

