## **7.3 Time Period for Reporting AE and SAE**

For each patient the standard time period for collecting and recording AE and SAEs will begin at start of study treatment and will continue throughout the hospital stay.

During the course of the study all AEs and SAEs will be proactively followed up for each patient; events should be followed up to resolution, unless the event is considered by the investigator to be unlikely to resolve due to the underlying disease. Every effort should be made to obtain a resolution for all events, even if the events continue after discontinuation/study completion.

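### The maternal symptom list has no stated reading before IMP, so subjective symptoms already present in labor can enter the side-effect table in both arms and blur the comparison

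*Protocol*

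**What the plan says.** Three rules govern what counts as present before treatment and what counts as an adverse event.

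- **History.** Protocol 6.2: "Significant findings that are present prior to the signing of informed consent must be included in the" CRF page for medical history or current condition. The flow chart in 5.1 marks medical history at screening only. Section 5.2.1 also places history in labor: "Baseline is defined as the time point in labor when slow progress is detected", and at that point "vital signs from mother and fetus will be obtained, and we will perform baseline observations regarding medical history".
- **Adverse events.** Protocol 7.3: "collecting and recording AE and SAEs will begin at start of study treatment". The flow chart has its first maternal adverse event mark in the column where IMP is given. Section 7.4 describes duration by the date of onset and the date of end.
- **Symptom list.** Protocol 5.2 has patient-reported maternal side effects entered in the CRF from a list: "Occurrence, degree and duration of side effects will be registered within 30 minutes after the treatment is given".

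The time of consent is given in two ways. Section 5.2: "All participating women will sign an informed consent during pregnancy". Section 3.1: "At this time, women may give informed consent to participate, or they can be included when they arrive at the delivery ward".

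Other measures do have a value before treatment. Maternal pulse and blood pressure and the CTG are marked at baseline in the flow chart, and pain on the VAS is taken before treatment (5.2, 5.2.1).

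**The concern.** Several of the drug effects named in 1.5 and 7.4 are subjective: dry mouth, dizziness, flushing, visual disturbance. Labor itself may cause some of them. If the list is asked only after the injection, a woman who already had a dry mouth answers yes, and nothing recorded beforehand shows that the symptom is old. A date of onset does not help when the symptom began and the injection was given on the same day.

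The tolerability table would then mix background symptoms of labor with new ones. Background symptoms are equally likely in both arms, so they pull the risk ratio toward 1 and widen the interval around the difference. They also leave the individual causality grade without a pre-dose record to rest on. Section 1.3 quotes a review that found the evidence on safety of these drugs insufficient, so a clear placebo-controlled comparison of side effects is worth having.

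**Working it through.** **1. Where the records meet.** The rule in 6.2 covers findings before consent, and 7.3 covers events from the start of treatment. For a woman who consents in pregnancy, a finding that begins between consent and IMP falls under neither rule. Section 5.2.1 could fill part of this interval, because it takes history observations in labor, but it names no symptom list and does not match the flow chart. For a woman who consents on arrival (3.1), the interval lies within a single admission.

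**2. Which measures lack a pre-IMP value.** Pulse, blood pressure, CTG and VAS pain have one. The listed subjective symptoms have none stated.

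**3. Size.** The plan gives no figure on this point to reproduce, neither a rate of symptoms before IMP nor a placebo rate. The sample size in 9.1 is not affected. The inputs are:

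- n = 125 per arm: 250 women (9.1), allocated 1:1 (9.2.1)
- b, the share with the symptom before IMP, equal in both arms: assumed 20%, range 10% to 40%
- new onset among women free of the symptom: assumed 2% on placebo and 12% on drug

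Formulas:

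- recorded risk as written = b + (1 − b) × new onset, if every prior symptom is recorded
- new onset counted over all women in the arm = (1 − b) × new onset
- 95% half-width = 1.96 × √[(p₀(1 − p₀) + p₁(1 − p₁)) / 125]

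At b = 20%, as written:

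- placebo 0.20 + 0.80 × 0.02 = 21.6%
- drug 0.20 + 0.80 × 0.12 = 29.6%
- difference 8.0 points, ratio 1.37
- half-width 1.96 × √[(0.1693 + 0.2084) / 125] = 10.8 points

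At b = 20%, new onset only:

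- placebo 0.80 × 0.02 = 1.6%
- drug 0.80 × 0.12 = 9.6%
- difference 8.0 points, ratio 6.0
- half-width 1.96 × √[(0.0157 + 0.0868) / 125] = 5.6 points

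Over the range of b, with the same onset rates:

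| b | As written | Difference | Ratio | Half-width | New onset only | Ratio | Half-width |
|---|---|---|---|---|---|---|---|
| 10% | 11.8% vs 20.8% | 9.0 | 1.76 | 9.1 | 1.8% vs 10.8% | 6.0 | 5.9 |
| 20% | 21.6% vs 29.6% | 8.0 | 1.37 | 10.8 | 1.6% vs 9.6% | 6.0 | 5.6 |
| 40% | 41.2% vs 47.2% | 6.0 | 1.15 | 12.3 | 1.2% vs 7.2% | 6.0 | 4.9 |

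The difference over all women is the same under both counts. It is smaller, by the factor 1 − b, than the 10-point difference among women free of the symptom before IMP. What the pre-IMP list restores is the ratio and the precision.

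**4. Sensitivity to the drug rate.** The assumed 12% lies above the band that 1.5 calls common (at least 1/100, below 1/10). With b = 20% and 2% on placebo:

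- 10% on drug: difference 6.4 points, half-width 10.7 as written and 5.2 for new onset only
- 5% on drug: difference 2.4 points, half-width 10.4 as written and 4.1 for new onset only

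Precision improves in each case. At 5% on drug, the interval would include zero under either count.

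**The case against.** - **The history is not closed at consent.** A reader might infer from 6.2 that nothing after consent can enter the history page, and that this is always weeks before labor. The text does not support this. Section 6.2 sets a minimum, 5.2.1 takes history observations in labor, and 3.1 allows consent on arrival. This stands. What remains is that the sections do not agree with each other.
- **Miscounting is not prescribed.** A reader might infer that earlier symptoms are counted as side effects. No section says so. Adverse events start at treatment, and the causality grade 'Unrelated' in 7.4 covers events that come too early. This stands as far as it goes: such symptoms can be recorded, which is less than saying that they are. The grading is a weak filter, since the person grading has no pre-dose symptom record and only a date of onset.
- **Heart rate is safe.** The synopsis names fetal and maternal heart rate as the safety assessments, and both have values before IMP. This stands; the gap concerns subjective symptoms only.
- **No test is planned.** Section 9.5.5 limits safety analysis to description, so rates of detection by a significance test would describe something nobody will run. This stands, and the size is given here as interval width only.
- **The definition may sit elsewhere.** Counting new or worse symptoms is commonly left to the SAP, and the CRF is not shown. True, but an SAP cannot recover a pre-dose reading that was never taken, and 5.2 fixes the timing of the list as after treatment.

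**Conclusion.** The point holds as a minor one. As written, the protocol states no reading of the maternal symptom list before IMP and records onset by date only. Subjective symptoms present in labor before the injection therefore cannot be reliably separated from new ones on the same day.

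Under blinded 1:1 allocation this is dilution and noise. A reader might infer a bias toward finding harm, but background symptoms fall equally on both arms and create no false difference. The illustrated gain, a half-width of about 5.6 instead of 10.8 points, rests on assumed rates (20% background, 2% against 12% new onset) and on every earlier symptom being recorded as a side effect. If 7.4 grading removed some of them, the loss would be smaller. The illustration also leaves worsening of an existing symptom aside.

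**What to change.** 1. In 5.2 and 5.2.1, register the same maternal symptom list once just before IMP, after the baseline VAS.
2. In 7.4, record onset by clock time as well as date.
3. Tabulate symptoms that are new or worse after IMP, by arm.
4. In 6.2, extend the history or current condition page to findings present before IMP, so that it ends where 7.3 begins.
5. Reconcile 3.1 with 5.2 on the time of consent, and the flow chart in 5.1 with 5.2.1 and 6.2 on the time of medical history.

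The cost is wording in the protocol and CRF and one short extra set of questions in labor. Asking about side effects beforehand may draw attention to them, but equally in both arms, and placing the questions after the baseline VAS keeps that pain score undisturbed. Treatment, endpoints and sample size do not change.

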### **6.3 Other Assessments**

The study participants will complete a questionnaire that examines experience of labor and birth one month after delivery (36).

## **7 SAFETY MONITORING AND REPORTING**

The investigator is responsible for the detection and documentation of events meeting the criteria and definition of an adverse event (AE) or serious adverse event (SAE). Each patient will be instructed to contact the investigator immediately should they manifest any signs or symptoms they perceive as serious.

The methods for collection of safety data are described below.

### **7.1 Definitions**

#### **7.1.1 Adverse Event (AE)**

An AE is any untoward medical occurrence in a patient administered a pharmaceutical product and which does not necessarily have a causal relationship with this treatment.

An adverse event (AE) can therefore be any unfavorable and unintended sign (including an abnormal laboratory finding), symptom, or disease temporally associated with the use of a medicinal (investigational) product, whether or not related to the medicinal (investigational) product.

The term AE is used to include both serious and non-serious AEs.

If an abnormal laboratory value/vital sign is associated with clinical signs and symptoms, the sign/symptom should be reported as an AE and the associated laboratory result/vital sign should be considered additional information that must be collected on the relevant CRF.

#### **7.1.2 Serious Adverse Event (SAE)**

Any untoward medical occurrence that at any dose:

- Results in death
- Is immediately life-threatening
- Requires in-patient hospitalization or prolongation of existing hospitalization
- Results in persistent or significant disability or incapacity
- Is a congenital abnormality or birth defect
- Is an important medical event that may jeopardize the participant or may require medical intervention to prevent one of the outcomes listed above.

Medical and scientific judgment is to be exercised in deciding on the seriousness of a case. Important medical events may not be immediately life-threatening or result in death or hospitalization, but may jeopardize the participant or may require intervention to prevent one of the listed outcomes in the definitions above. In such situations, or in doubtful cases, the case should be considered as serious. Hospitalization for administrative reason (for observation or social reasons) is allowed at the investigator's discretion and will not qualify as serious unless there is an associated adverse event warranting hospitalization.

A pre-planned hospitalization admission (i.e., elective or scheduled surgery arranged prior to the start of treatment) for pre-existing condition is not considered to be a serious adverse event.

### **7.1.3 Suspected Unexpected Serious Adverse Reaction (SUSAR)**

Suspected Unexpected Serious Adverse Reaction: SAE (see section 8.1.2) that is unexpected as defined in section 8.2 and possibly related to the investigational medicinal product(s).

## **7.2 Expected Adverse Events**

Expected AEs are: Maternal flushing, maternal tachycardia, fetal tachycardia. Other AEs are described in the SmPC.

## **7.3 Time Period for Reporting AE and SAE**

For each patient the standard time period for collecting and recording AE and SAEs will begin at start of study treatment and will continue throughout the hospital stay.

During the course of the study all AEs and SAEs will be proactively followed up for each patient; events should be followed up to resolution, unless the event is considered by the investigator to be unlikely to resolve due to the underlying disease. Every effort should be made to obtain a resolution for all events, even if the events continue after discontinuation/study completion.

## **7.4 Recording of Adverse Events**

If the patient has experienced adverse event(s), the investigator will record the following information in the CRF:

- The nature of the event(s) will be described by the investigator in precise standard medical terminology (i.e. not necessarily the exact words used by the patient).
- The duration of the event will be described in terms of event onset date and event ended data.
- The intensity of the adverse event will be described as mild, moderate and severe.
  - Mild; asymptomatic or mild symptoms; clinical or diagnostic observations only; intervention not indicated.
  - Moderate; minimal, local or noninvasive intervention indicated; limiting age-appropriate instrumental Activities of Daily Living.
  - Severe or medically significant but not immediately life-threatening; hospitalization or prolongation of hospitalization indicated.
- Specifically, mild AEs include dryness of the mouth, transient tachycardia and flushing. Moderate AEs include visual disturbances, urinary retention, and fall in blood pressure and skin reactions. SAEs include dyspnea, anaphylactic reactions, serious skin reactions including Steven-Johnson and anaphylactic shock.
- The Causal relationship of the event to the study medication will be assessed as one of the following:

**Unrelated:**

There is not a temporal relationship to investigational product administration (too early, or late, or investigational product not taken), or there is a reasonable causal relationship between non-investigational product, concurrent disease, or circumstance and the AE.

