Maternal: Common ( $\geq 1/100$  to  $< 1/10$ ): Gastrointestinal: Dryness in the mouth. Cardiology: Tachycardia, dizziness. Ophtalmology: Accomodation disturbance. Unknown frequency: Cardiology: Hypotension, flushing. Skin: Dyshidrosis. Immune system: Anaphylactic shock, anaphylactic reactions, dyspnea, skin reactions including urticarial, rash, erythema and itching. Other forms of hypersensitivity. Kidney: Urinary retention. Ophtalmology: Mydriasis, increased intraocular pressure. Rare cases with serious skin reactions like Steven-Johnsons syndrome have been reported.

According to WHO recommendations for augmentation of labor based on the Cochrane review from 2013 (22),(31), there are 5 RCTs comparing Buscopan with placebo including altogether 845 newborns with no differences in transfer to the Neonatal Intensive Care Unit. One RCT with 100 fetuses did not show any differences in prevalence of fetal distress. One RCT with 130 fetuses did not show any difference in fetal bradycardia, and two RCTs with 230 fetuses did not show any difference in fetal tachycardia. None of the 17 RCTs in the Cochrane review reported any side effects related to Buscopan (22).

Women who are allocated to the control group will contribute to answer an important medical question for future laboring women and their children. They will need an IV access, which could be considered a down side. However, it is routine procedure in the hospital to establish an IV line

when there is labor dystocia. The IV access may be an advantage if they women augmentation with oxytocin or if something unexpected happens.

Women who are allocated to the intervention group may experience a shorter labor if the IMP has the presumed effect. In that case, they will receive less oxytocin, and experience fewer oxytocin side effects. Based on previous studies, the reduction in the active phase of labor will be approximately one hour. This reduction will take place in the first stage (opening phase), and not the second stage of labor (expulsion phase).

Based on data from our department, 72% of primiparous women who crossed the alert line (the inclusion criterion of this study) of the partogram received augmentation with oxytocin with an average duration of 214 minutes. Of the women who crossed the alert line, 15% delivered by cesarean section and 25% had an operative vaginal delivery, compared to 2% and 16% among women with normal progress in labor, respectively.

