**Unlikely:**

There is a temporal relationship to investigational product administration, but there is not a reasonable causal relationship between the investigational product and the AE.

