**Possible:**

There is reasonable causal relationship between the investigational product and the AE. Dechallenge information is lacking or unclear.

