**Definite:**

There is a reasonable causal relationship between the investigational product and the AE.

- Action taken
- The outcome of the adverse event – whether the event is resolved or still ongoing.

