### **7.5.2 SUSARs**

SUSARs will be reported to the Competent Authority according to national regulation. The following timelines should be followed:

The sponsor will ensure that all relevant information about suspected serious unexpected adverse reactions that are fatal or life-threatening is recorded and reported as soon as possible to the

Competent Authority in any case no later than seven (7) days after knowledge by the sponsor of such a case, and that relevant follow-up information is subsequently communicated within an additional eight (8) days.

All other suspected serious unexpected adverse reactions will be reported to the Competent Authority concerned as soon as possible but within a maximum of fifteen (15) days of first knowledge by the sponsor.

In order to avoid unnecessary unblinding of study personnel, an independent person at the Clinical Trial Unit at Oslo University Hospital, will unblind before sending to Competent Authority

SUSARs will be reported using the CIOMS form.

Reference Safety Information: No SARs are expected by the sponsor for the purpose of expedited reporting of SUSARs in this clinical trial, i.e. all adverse events that have a reasonable possibility of a causal relationship with the IMP and are “serious” will be reported as SUSARs.

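### The causality scale in section 7.4 lets the same adverse event be both Unrelated and Possible when the IMP and another cause are each reasonable, and no rule says which prevails

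*Protocol*

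**What the plan says.** Section 7.4 (Recording of Adverse Events) sets the rule for choosing a category: "The Causal relationship of the event to the study medication will be assessed as one of the following". Five levels follow.

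- *Unrelated*: no temporal relationship to the IMP, "or there is a reasonable causal relationship between non-investigational product, concurrent disease, or circumstance and the AE".
- *Unlikely*: the timing fits, but the IMP is not judged a reasonable cause.
- *Possible*: "There is reasonable causal relationship between the investigational product and the AE. Dechallenge information is lacking or unclear".
- *Probable*: a reasonable IMP relationship, and the event responds to dechallenge.
- *Definite*: "There is a reasonable causal relationship between the investigational product and the AE", with no further condition.

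Relatedness is used again in two places. Section 7.1.3 makes possible relation to the IMP part of the SUSAR definition. Section 7.5.2 treats no serious reaction as expected, so "all adverse events that have a reasonable possibility of a causal relationship with the IMP" and are serious are to be reported as SUSARs. Under section 7.5.1 each SAE goes to the medical officer, who makes a separate evaluation of causality and expectedness.

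Two features of the design bear on this. The IMP is one intravenous dose (section 4.3), and section 4 (The intervention group) allows it to be given together with oxytocin.

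**The concern.** A scale from which one level must be chosen needs levels that exclude each other, or a rule of precedence. This one has neither at the boundary that matters, between not related and related. The lowest level is reached through the existence of another reasonable cause, without asking whether the IMP is also one. Labor supplies many other causes, and oxytocin is part of standard care in both arms.

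Two assessors who agree on every fact of a case could record *Unrelated* and *Possible* respectively, and both would be following the protocol. For a serious event, the recorded category could then contradict the reporting standard in sections 7.1.3 and 7.5.2. Because 7.5.2 treats no serious reaction as expected, causality is the only filter left between an SAE and an expedited report.

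**Working it through.** The protocol gives no figure on this point, so the check is one of logic.

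**Conditions.** Let T = a temporal relationship to the IMP, I = the IMP is a reasonable cause, O = another product, disease or circumstance is a reasonable cause, and D = dechallenge information is lacking or unclear.

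**Definitions in section 7.4, restated.**

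- Unrelated = (not T) or O
- Unlikely = T and not I
- Possible = I and D
- Probable = I and a response to dechallenge
- Definite = I

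**Events that follow the IMP in time (T true), with D true.** After a single bolus there is no continuing treatment to withdraw, so D will often hold.

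| I | O | Levels met |
|---|---|---|
| yes | no | Possible, Definite |
| yes | yes | Unrelated, Possible, Definite |
| no | yes | Unrelated, Unlikely |
| no | no | Unlikely |

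Only the last row gives a single level. The second row is the one that matters, because its levels straddle the line between related and not related. The third row is harmless for reporting, since both levels deny an IMP relationship. In the first row both levels assert one, so reporting is again unaffected, but *Definite* has no criterion that sets it apart.

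**Can the second row occur in this trial?** Section 1.5 lists side effects for both drugs. Four entries are common to the two lists:

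| Event | Oxytocin list | Butylscopolamine list |
|---|---|---|
| Tachycardia | common | common |
| Urinary retention | unknown frequency | unknown frequency |
| Rash | rare | unknown frequency |
| Anaphylactic reaction | rare, with dyspnea, hypotension or shock | unknown frequency |

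Dyspnea, hypotension and shock stand in the oxytocin list only as features of the anaphylactic reaction, so they are not counted separately. With simultaneous administration permitted, an event of any of these types can have two reasonable causes.

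**Effect of the added condition.** If Unrelated becomes (not T) or (O and not I), the second row loses *Unrelated* and keeps only levels that assert an IMP relationship. The straddle is gone.

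**The case against.** The strongest reply is that expedited reporting does not run through the 7.4 category. Section 7.5.2 states its own test and does not refer back to 7.4, so a serious event that the IMP could reasonably have caused meets it whether or not oxytocin is another candidate. Every SAE is also reported within 24 hours and receives the medical officer's causality evaluation, whatever the investigator recorded. This stands in large part. A reader might infer that SUSARs will be lost; the protocol does not support that. What remains is that no rule says which assessment prevails when the investigator and the medical officer differ, and that the second evaluation is stated for SAEs only.

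Other stronger readings also fail.

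- Section 1.5 says that "72% of primiparous women who crossed the alert line" received oxytocin, and a reader might take this as the share of women exposed to the conflict. It counts oxytocin at any time in labor. The IMP is given soon after the alert line is crossed, and oxytocin may start well afterwards. *Unrelated* also asks for a reasonable causal relationship with the other product, so exposure plus a listed side effect is not enough.
- The one shared reaction that 7.4 names as an SAE is graded rare for oxytocin, below 1 in 1,000. Even if all 250 women received oxytocin, fewer than 250 × 0.001 = 0.25 oxytocin-caused cases would be expected. That bounds cases caused by oxytocin. It does not bound cases caused by the IMP in which oxytocin is a plausible rival.
- A reader might expect a distorted table of related events. Section 9.5.5 promises descriptive tabulations and names none by relatedness. All AEs are recorded regardless of causality, so tables of all events by arm are untouched.
- It would be too much to say that every IMP-attributable event is both *Possible* and *Definite*. Section 1.5 calls the anticholinergic effects transient, and an assessor might record their resolution as dechallenge.

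**Conclusion.** The defect is real and lies in what the protocol states; it is not detail left to a later document. *Unrelated* and *Possible* are not mutually exclusive although one level must be chosen, and this is at odds with the relatedness standards in sections 7.1.3 and 7.5.2.

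The consequence is a risk of misclassification and an unresolved conflict between sections. For serious events the risk is reduced by 7.5.2 and 7.5.1; for non-serious events no second review is stated. Its frequency cannot be derived from the protocol, because nothing gives the overlap in time between IMP and oxytocin or how assessors would read the definition. Sample size, power, alpha and the efficacy analyses are not affected. The conclusion assumes that the definitions are applied as written; an assessor who silently adds the missing condition would avoid the problem. The change should be made because it is a short wording correction.

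**What to change.** 1. In *Unrelated*, make the second limb conditional: another cause explains the event and the IMP is not a reasonable cause of it.
2. State that an event for which both the IMP and something else are reasonable causes is scored at least *Possible*.
3. State that *Possible*, *Probable* and *Definite* all count as related for section 7.5.2.
4. State that where the investigator and the medical officer differ, the more conservative assessment (the one closer to relatedness) governs reporting.
5. Optionally, give *Definite* a criterion of its own or merge the top levels. The main defect is cured without this.

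The cost is a change to section 7.4, a sentence each in 7.5.1 and 7.5.2, and matching text on the AE and SAE forms. No new data are collected. The downside is that slightly more events will be classed as related and, when serious, assessed for expedited reporting.
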